##### **Exclusion criteria**

- Diagnosed with diabetes mellitus according to the WHO criteria
- Anti-diabetic medication
- Active liver disease

- At screening or at any subsequent visit a level of aspartate aminotransferase (ASAT) or alanine aminotransferase (ALAT) of more than three times the upper limit of the normal range
- Gastrointestinal ailments which may interfere with the ability to adequately absorb sulforaphane
- At screening visit creatinine > 130 µmol/L
- Coagulation disorder or current anti-coagulant therapy, which may be affected by the BSE
- Diagnosed with a cardiovascular disease or known cardiovascular event, transient ischemic attack, coronary by-pass surgery or other coronary vessel intervention within 6 months prior to enrolment
- Systemic glucocorticoid treatment
- Herbal treatment, defined as food supplement (except multivitamin treatment) with herbal or vegetable extracts that may affect blood glucose
- Allergy to broccoli
- Participant unable to understand the study information
- Participation in other clinical trial which may affect the outcome of the present study
- Any other physical or psychiatric condition or treatment that in the judgment of the investigator makes it difficult to participate in the study.

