#### **Criteria for withdrawal**

- The participant can withdraw from the study at any time without further motivation and without any consequences for his/her future treatment.
- The participant will be withdrawn should they develop any condition or begin taking any compound that is part of the exclusion criteria.
- A participant can be withdrawn if he/she does not adhere to the procedures as specified in the protocol. No extra financial or treatment compensation is given to the participant in that case.
- If the participant experience serious adverse events, and there are reasons to think that the event is related to the study, he/she will be immediately withdrawn and prompt action will be taken to assist the participant as necessary.
- The study can be stopped at any time due to a lack of treatment effect, side effects or that the procedures of the protocol are not adhered to. In that case all participants as well as relevant authorities will be notified.

All participants that are withdrawn will continue their regular medication and their ordinary physician will be notified as appropriate.

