### **4.3 Effect variables**

#### **The primary effect variable:**

Venous fasting blood glucose. Venous fasting blood glucose will be analysed at screening visit (only participants having capillary glucose 6.0-6.9 mmol/l), visit 2 and 3 and used for effect analyses.

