#### **5.4 Compliance**

The participants should return any remaining capsules at visit 3. Only participants who have taken >75% of their capsules during the total study period and >80% during the last month will be included in the per protocol analyses. This is calculated by (the number of delivered bags – number of returned bags) / number of days in the study.

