## **6. STATISTICS AND DATA HANDLING**

### **6.1 Statistics**

The primary effect variable is venous fasting blood glucose. Participants will be analysed using intraindividual one-tailed comparisons before and after treatment and compared between the placebo and BSE arms using Student's t-test. The study hypothesis is that participants taking BSE for 12 weeks will have at least 0.3 mM lower fasting blood glucose on average than participants taking placebo. The intra-individual standard deviation of fasting blood glucose is 0.63 mM, based on analyses in our longitudinal cohorts of subjects with impaired fasting blood glucose. We therefore need 37 participants in each randomization group to detect a difference of 0.3 mM in fasting blood glucose between the groups at 80% power at  $p < 0.05$ . We aim to recruit 50 participants in each group to cover for potential dropouts.

We will also make a subgroup analysis of participants with fasting triglycerides above median. This is based on our previous study on BSE (Axelsson et al.) showing that BSE is particularly effective in individuals with increased triglyceride levels. It is known that increased triglycerides are more common in subjects with elevated fatty liver content (Gastaldelli et al., 2009) and we therefore want to investigate whether this subgroup of the population would benefit more from BSE.

Both Intention-to treat (ITT) and per protocol (PP) analysis of the outcome variables will be performed and ITT will be used as a basis for the conclusions. Missing values will be replaced by the latest value available. Participants with poor compliance (see 5.4) will however not be included in any analyses.

The secondary study variables, HbA1c, fatty liver index, fasting lipids, free fatty acids, insulin, HOMA-IR and weight, will be analysed using intraindividual comparisons between visit 2 and 3.

We will later analyse stool samples to investigate changes in abundance of bacterial strains between the BSE and placebo groups.

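### Carrying the latest value forward gives anyone without visit 3 who stays in the ITT analysis a pre-treatment glucose, which biases the primary estimate

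*Protocol*

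**What the plan says.** Section 6.1 of the protocol states the rule for missing data, "Missing values will be replaced by the latest value available", and says that "ITT will be used as a basis for the conclusions". The next sentence limits who is in the data at all: "Participants with poor compliance (see 5.4) will however not be included in any analyses".

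Section 4.3 fixes when the primary variable is measured. It begins "Venous fasting blood glucose will be analysed at screening visit" and adds visits 2 and 3, all for use in the effect analyses. Product is handed out at visit 2 (section 3.4), so screening and visit 2 both precede treatment. Section 3.6 describes only a telephone call between visits 2 and 3. No blood sample at early termination is described.

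Three other rules decide who lacks visit 3 or leaves the analysis:

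- Withdrawal (section 3.2): "The participant will be withdrawn should they develop any condition or begin taking any compound that is part of the exclusion criteria". The exclusion list includes "Diagnosed with diabetes mellitus according to the WHO criteria" and anti-diabetic medication.
- Compliance (section 5.4): "Only participants who have taken >75% of their capsules during the total study period and >80% during the last month" qualify for the per-protocol analyses. Intake is computed as "the number of delivered bags – number of returned bags) / number of days in the study".
- Timing (sections 3.4 and 3.6): a participant whose visit 3 falls too late is excluded.

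**The concern.** Carrying the last observation forward is normally understood to carry the last value seen on treatment. Here no such value exists, so the rule is in effect baseline carried forward. The imputed figure says nothing about what happened after randomisation, yet it enters the t-test as if it had been observed.

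Zero is also not a neutral guess. Entry requires a venous value of 6.1-6.9 mM at both screening and visit 2, so some fall towards the population mean is expected at visit 3 even on placebo. Imputed participants are denied that fall and completers are not.

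At stake is the primary ITT estimate and its interval, on which the conclusions rest. The rule is stated in the protocol itself, so it is not a detail left open for an analysis plan.

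**Working it through.** **Inputs from the protocol.** Section 6.1 gives a difference of 0.3 mM, SD 0.63 mM, 37 needed and 50 recruited per group, and a one-tailed comparison. Sections 3.3 and 3.4 give the entry window of 6.1-6.9 mM.

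**Assumptions.** The stated SD of 0.63 is taken as the SD of individual change. No dropout rate is stated; the recruitment margin implies (50 − 37)/50 = 26%, and 37/(1 − 0.26) = 50 reproduces the stated total.

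**1. What a missing visit 3 becomes.** The latest value is visit 2. With visit 2 as baseline, change = visit 2 − visit 2 = 0. If the baseline were the mean of screening and visit 2, the imputed change would be (visit 2 − screening)/2. With both values in 6.1-6.9, that lies within ±(6.9 − 6.1)/2 = ±0.4 mM. Either way it holds no post-treatment information.

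**2. Equal loss d in both arms, all imputed, visit-2 baseline.** Expected difference = (1 − d) × 0.30, taking placebo change as 0. Power is one-sided, by normal approximation.

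| d | Difference (mM) | Power, carried forward | Power, completers only |
|---|---|---|---|
| 0% | 0.30 | 76.9% | 76.9% |
| 10% | 0.27 | 72.6% | 73.0% |
| 20% | 0.24 | 67.8% | 68.6% |
| 26% | 0.222 | 64.6% | 65.7% |

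**3. Interval coverage at d = 26%.** The variance of change is 0.74 × 0.63² = 0.294 on placebo. On BSE it is 0.74 × (0.63² + 0.30²) − 0.222² = 0.311. The standard error is √((0.294 + 0.311)/50) = 0.110. A 95% interval contains 0.30 only if the estimate exceeds about 0.30 − 1.98 × 0.110 = 0.082, which lies (0.222 − 0.082)/0.110 = 1.27 standard errors below its mean. Coverage is therefore a little under 90%; simulation gives about 89%.

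**4. Unequal loss, no true effect.** Let both arms fall by m without treatment. The spurious difference is m times the difference in the shares observed. With m = 0.2 mM (assumed) and 26% loss on placebo against 10% on BSE, it is 0.90 × 0.2 − 0.74 × 0.2 = 0.032 mM in favour of BSE. With the arms swapped it is 0.032 mM against BSE. Simulated one-sided error is about 8.5% in the first case and 2.5% in the second, against a nominal 5%. For m from 0.05 to 0.35 mM, the unfavourable case runs from about 6% to 12%. That range of m comes from simulating selection on two readings of 6.1-6.9 mM, with assumed between-person SD 0.5-0.6 and within-person SD 0.25-0.63.

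**5. Who is imputed and who is deleted.** With the 84 planned days as denominator and unused bags returned, stopping at week 4 gives 28/84 = 33%, week 8 gives 67% and week 9 gives 75%. All miss the requirement of more than 75%, so these participants are removed. With days actually spent in the study as denominator, the same people can pass and be imputed. The protocol does not define the denominator for a dropout.

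**6. Withdrawal for new diabetes.** If k such participants in an arm of 50 stay in the analysis without visit 3, and their true rise is r, that arm's mean is understated by k × r/50. For an assumed r of 0.5-1.0 mM, this is 0.01-0.02 mM for k = 1 and 0.05-0.10 mM for k = 5.

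**The case against.** The best defence is that little harm follows in the likeliest case. Under equal loss the test keeps its 5% size, power is close to that of completers only, and the dilution works against BSE. The null bias is about a tenth of the 0.3 mM target. It needs an assumed 16-point imbalance in loss and an assumed regression to the mean. The gastrointestinal effects anticipated in section 7.1 give no reason to expect more loss on placebo. All of that stands and limits the size of the point. It does not rescue the estimate or its interval.

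A reader might infer four stronger things that the protocol does not support:

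- **Every dropout is scored as unchanged.** Section 6.1 removes poor compliers from all analyses, and late visits are excluded. Only dropouts kept in ITT are affected.
- **The change is always exactly zero.** That needs visit 2 as baseline. The protocol states a visit 2 to visit 3 comparison only for the secondary variables, and section 4.3 also brings screening glucose into the primary analysis.
- **The standard error is falsely small.** Under equal 26% loss and no effect it is 0.108, against 0.63 × √(2/37) = 0.146 for completers. But the estimate is itself multiplied by 0.74, and 0.74 × 0.146 = 0.108. In simulation the true spread of the estimate was also 0.108. The error lies in what is estimated, not in its reported precision.
- **Many diabetic conversions are hidden.** The trial measures no glucose between visits 2 and 3, so a diagnosis in that period would have to come from outside care, and a rise seen at visit 3 is used. This is a secondary point.

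It is also fair that the full specification of an imputation model belongs in an analysis plan. The protocol, however, names a rule, and that rule is unsuitable.

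**Conclusion.** The concern holds for participants who lack visit 3 and stay in the ITT analysis. They receive a pre-treatment glucose, so the primary estimate is biased. Equal loss dilutes it in proportion to the share imputed. The fall from 0.30 to 0.22 mM, with coverage of about 89%, is an upper-end figure: it assumes that the whole inferred 26% is imputed, that visit 2 is the baseline and that the SD of change is 0.63 mM. Unequal loss can add a small bias whose direction depends on which arm loses more. The 0.03 mM and the one-sided errors of about 8.5% and 2.5% rest on the assumed 0.2 mM fall and the assumed 26% against 10% loss. A participant withdrawn for diagnosed diabetes or new anti-diabetic medication, if kept without visit 3, would count as unchanged in a trial whose outcome is glucose. The number of such cases cannot be estimated from the protocol.

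**What to change.** Replace the carry-forward sentence in section 6.1. The primary ITT analysis should model visit-3 glucose using the screening and visit-2 values already collected. Missing visit-3 values should be handled under missing-at-random, by a mixed model on the three measurements or by multiple imputation within arm. Add one sensitivity analysis that penalises missing BSE values, because missing-at-random cannot be checked and loss may depend on glucose. Keep carry-forward at most as a further sensitivity analysis.

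Separate stopping product from leaving follow-up. Without changing when product is stopped, still invite those participants to the visit 3 already planned, and use the value. This recovers the information that no imputation can supply, including for participants withdrawn because of new diabetes or new medication.

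The cost is a change of protocol wording, modest extra analysis work, and keeping an existing visit for the few who stop early. No new measurement is needed.

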### **3.6 Between visit 2 and 3**

Participants are instructed to take their BSE/placebo daily in the morning starting 12 weeks before visit 3. They have a paper attached on the box with their medication/placebo where they tick each day they have taken a dose. They will receive a slight surplus, in case they for some reason have to postpone visit 3. The reason is that we want to avoid gaps between the last intake and visit 3. If a participant or the study team with short notice have to cancel visit 3, e.g. due to illness, and the participant runs out of study medication we must have a buffer so that the treatment can continue daily until visit 3. The total treatment time can under no circumstances be more than 15 weeks, and if visit 3 has to be postponed beyond that limit the participant will be excluded. Any remaining doses should be brought back to the study team at visit 3.

The study team will contact the participants by phone 2-4 weeks after the initiation of the treatment to ask whether they experience any side effect and to check compliance. Moreover, information on changes in use of pharmaceutical drugs is collected. Reasonable efforts should be undertaken to get into contact with the participants by calling back if no reply, leaving messages and as a second option sending emails. Participants are also instructed to contact us in case they have any suspected side effects of the treatment.

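### Section 6.1 removes poor compliers from every analysis, so the ITT set on which the conclusions rest is filtered by the protocol's only stated per-protocol criterion

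*Protocol*

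**What the plan says.** Protocol section 6.1 plans both ITT and per-protocol analyses and ranks them: "ITT will be used as a basis for the conclusions". It then gives a missing-data rule, "Missing values will be replaced by the latest value available", and follows it with "Participants with poor compliance (see 5.4) will however not be included in any analyses".

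The cross-reference is to section 5.4, which sets the thresholds but gives them a narrower use. Its condition for a participant reads: "taken >75% of their capsules during the total study period and >80% during the last month will be included in the per protocol analyses".

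Other sections also deal with randomised participants who depart from the schedule. Section 3.6 says of the 15-week limit that "if visit 3 has to be postponed beyond that limit the participant will be excluded", and section 3.4 has a similar rule for a visit 3 that cannot be arranged in time. The withdrawal criteria in section 3.2 add: "A participant can be withdrawn if he/she does not adhere to the procedures as specified in the protocol".

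**The concern.** An ITT comparison is protected because the groups compared are the groups that were randomised. Compliance is known only after randomisation: bags are counted when they are returned at visit 3. A set chosen on compliance is therefore a set chosen on something the treatment may have influenced, and the two arms need no longer be comparable.

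The sentence in 6.1 applies that selection to every analysis, including the one that carries the conclusions. It also weakens the check that the protocol sets up by planning two analysis sets. Compliance is the only per-protocol criterion stated, so if it filters the ITT set as well, agreement between the two results says little about robustness to non-adherence.

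A later analysis plan cannot settle this by itself. If it follows 6.1 it inherits the defect, and if it follows 5.4 it contradicts 6.1.

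**Working it through.** **1. The text side by side**

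| Place | Rule | Set affected |
|---|---|---|
| 6.1, ranking of analyses | ITT is the basis for the conclusions | ITT |
| 6.1, last sentence of that paragraph | Poor compliers left out | All analyses, so ITT too |
| 5.4 | More than 75% of doses overall and more than 80% in the last month | Per-protocol only |
| 3.4, 3.6 | Participant excluded if visit 3 falls too late | Not stated (participation or analysis) |

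The second row conflicts with the first and with the third. No other section brings poor compliers back into any analysis.

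**2. The protocol's own figures**

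The protocol gives no expected rate of poor compliance, so there is no figure of its own to reproduce on this point. The nearest is the recruitment margin, 50 per group to retain 37: (50 − 37)/50 = 0.26. This margin is described as cover for dropouts, not for poor compliers.

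The 37 itself does not come from a two-group t-test with a difference of 0.3 mM and SD 0.63 mM, which needs 71 per group two-sided or 56 one-sided. A one-sample two-sided t-test gives 36.6, rounded up to 37. That is a separate matter and nothing below depends on it.

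**3. Formula for the bias**

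For one arm, let *e* be the share excluded and *g* the mean change in poor compliers minus the mean change in good compliers, so that positive *g* means poor compliers do worse.

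- Mean of all randomised = mean of good compliers + *e* × *g*.
- So mean of good compliers = mean of all randomised − *e* × *g*.
- BSE minus placebo among good compliers = the difference among all randomised − (*e*_BSE × *g*_BSE − *e*_placebo × *g*_placebo).

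With the same gap in both arms, the spurious benefit is (*e*_BSE − *e*_placebo) × *g*. It is zero if exclusion is unrelated to outcome, or if the shares are equal and the gaps are equal too. If placebo loses more participants than BSE, the sign reverses.

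**4. Numbers (all inputs assumed)**

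Spurious benefit in mM with no true effect:

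| Difference in share excluded | Gap 0 | Gap 0.3 | Gap 0.4 | Gap 0.5 |
|---|---|---|---|---|
| 0 points | 0 | 0 | 0 | 0 |
| 5 points | 0 | 0.015 | 0.020 | 0.025 |
| 10 points | 0 | 0.030 | 0.040 | 0.050 |
| 20 points | 0 | 0.060 | 0.080 | 0.100 |

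The target in 6.1 is "at least 0.3 mM lower fasting blood glucose on average than participants taking placebo". The largest cell is 0.10/0.30, one third of it.

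**5. Effect on the test**

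This rests on 20,000 simulated t-tests with no true effect. It takes 0.63 mM as the SD of the change, 50 on placebo, exclusion from the BSE arm only, and a gap of 0.3 mM.

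| Share of BSE arm excluded | Spurious benefit (mM) | One-sided error at 0.05 | Two-sided error at 0.05 |
|---|---|---|---|
| 10% | 0.030 | 0.077 | 0.055 |
| 20% | 0.060 | 0.116 | 0.073 |
| 26% | 0.078 | 0.139 | 0.088 |

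**The case against.** The contradiction in the text is hard to contest, but a reader might draw four stronger inferences that the protocol does not support.

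- *The ITT and per-protocol sets become identical.* They need not. Under the carry-forward rule, a compliant participant without a visit 3 could remain in ITT, and 5.4 does not say whether the per-protocol set would keep that person. What stands is that the one stated per-protocol criterion is applied to both.
- *Intolerant or unresponsive BSE participants vanish while their placebo counterparts stay.* The rule applies to both arms, so poor compliers on placebo go too. Nothing shows how non-response would lead to poor compliance: participants are blinded, no glucose test is scheduled between visits 2 and 3, and the one planned phone call concerns side effects, compliance and drug changes.
- *Section 7.1 predicts differential intolerance.* It lists gastrointestinal symptoms as potential events and concludes that few adverse events, if any, are expected. It also cites a two-week study in which 199 of 200 subjects completed all doses without reporting any. An imbalance between arms is possible but is not forecast.
- *Late visit-3 values are being discarded from ITT.* The protocol plans no visit-3 value beyond the 15-week limit, and 3.4 and 3.6 do not say whether exclusion means from participation or from analysis. Such a participant could still enter ITT by carry-forward. What stands is a need for clarification.

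The sizes above are also open to challenge. No rate, imbalance or gap comes from the protocol, and a 0.5 mM gap is about 0.8 of the stated SD (0.5/0.63) and larger than the whole target effect. They show what could happen and do not estimate what will.

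Finally, the authors may have meant the exclusion for the per-protocol set only, as 5.4 says. That makes the correction easy, but 6.1 as written says otherwise.

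**Conclusion.** The point holds. Section 6.1 contradicts both section 5.4 and its own choice of ITT as the basis for conclusions. Followed literally, it conditions the primary comparison on compliance observed after randomisation. This needs correcting before analysis, because it concerns the primary analysis set and is stated outright, not left open.

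The case rests on the wording, not on a predicted bias. The size cannot be determined from the protocol. It is zero if exclusion is equal across arms and unrelated to outcome. Under a gap common to both arms, assumed differences of 0 to 20 percentage points and assumed gaps of 0 to 0.5 mM give 0 to 0.10 mM against a 0.3 mM target. The upper end would matter for the conclusion and the lower end would not, and the design cannot guarantee which applies.

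**What to change.** In section 6.1, replace the sentence on poor compliance with: *Participants with poor compliance (5.4) are excluded from the per-protocol analysis only.* Define ITT as all randomised participants in their assigned arm, regardless of compliance. State that exclusion under 3.4 and 3.6 does not remove a randomised participant from the ITT set. This leaves the visit window and the 15-week treatment limit untouched. Participants without a visit 3 would then fall under the missing-data rule already in 6.1, and whether that rule is adequate is a separate question.

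The textual cost is one replaced sentence, a definition and a clarification. The statistical cost is dilution, which comes with the ITT basis the protocol has already chosen. If 15% of the BSE arm got no benefit (assumed), a 0.30 mM effect would appear as 0.85 × 0.30 = 0.255 mM. At 20% it would be 0.80 × 0.30 = 0.24 mM, and with 50 per arm and SD 0.63 mM the two-sided power would fall from 65% to 47% (one-sided from 76% to 60%). Zero benefit is a pessimistic assumption, since someone just under the thresholds has still taken most doses.
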